## Abstract

**Background:**

Despite an initial steep decrease in alcohol misuse among Estonians through structural intervention means and the scaling up of alcohol counselling in the mid-2000’s, most of the country’s alcohol misuse indicators remain clearly higher than European averages. Consequently, an online self-help program was launched as part of an initial behavioral intervention initiative to foster progress in alcohol prevention on a population level.

**Methods:**

A two-arm randomized controlled trial (RCT) has been designed to compare the efficacy of a culturally-adapted minimal-guidance online self-help program, the 8-week “Selge” online program against a control condition that consists of a self-administered test of alcohol use and advice regarding usual treatment in Estonia. A target sample of 600 individuals will be recruited and randomly assigned to either condition. The program will contain 10 modules based on principles of cognitive behavioural therapy (CBT) and motivational interviewing (MI). Participants in the control group will have access to the full treatment after they complete their final follow-up assessment. The primary outcome will be change in the Alcohol Use Disorders Identification Test (AUDIT) score between the 6-month follow-up and baseline assessments. Secondary outcomes will include the number of standard drinks consumed and alcohol-free days, drinking motives and motivation for change, as well as changes in mental health. Assessments will be completed at baseline, at the end of treatment, and at 6 months follow-up. Data analysis will follow the intention-to-treat principle and employ (generalised) linear mixed models.

**Discussion:**

The *“Selge” program* is the first and only internet program for the intervention of alcohol misuse in Estonia. If proven effective, it will foster progress in the intervention of alcohol misuse in the Estonian population and be implemented as a standard program amidst the continuum of intervention and care.

**Trial registration:**

Current Controlled Trials ISRCTN48753339 registered 04/06/2019 retrospectively.

## Background

Misuse of alcohol is a worldwide problem that has numerous negative consequences for public health. The World Health Organization (WHO) sees 6 l of pure alcohol consumed per capita per year as significant damage to public health [1]. Relative to 2007, when the consumption of alcohol by Estonian residents reached a peak of 14.8 l of pure alcohol per adult (15-years-old and older) per year, by 2015 consumption had decreased by more than 4 l, though it remained at the level of roughly 10 l through 2016 and 2017 [2]. Moreover, the prevalence of heavy episodic drinking among people age 15–24 is still higher than the European Union average and the alcohol-attributable contribution to overall mortality, as a fraction, in Estonian adults is almost four times the European average [3].

As a consequence, the National Institute for Health Development and the Ministry of Social Affairs of Estonia compiled the so-called *Green Paper on Estonian Alcohol Policy* to reduce alcohol abuse and harm in 2014. This was followed by various initiatives that included the program “More Sober and Healthier Estonia”, funded by the European Social Fund. The aims of this program are to a) improve the availability and quality of services needed to prevent and treat alcohol abuse; and b) to raise public awareness about the risks of alcohol consumption and existing support services. In the area of health services, the program designates action in two directions: 1) early detection of alcohol abuse by family physicians; and 2) treatment of alcohol abuse by medical specialists. Over the period 2014–2018, 22 health centres provided early detection and an Alcohol Disorder Patient Treatment Guideline was compiled, which also shows patient pathways within the healthcare system. By 2018, nine facilities had started providing the treatment quickly and effectively [4].

Despite this progress, there is still a long way to go. The recent survey (2018) on health behaviour shows that 14,7% of Estonian adults consume alcohol at a health threatening/ damaging alcohol level, while only 1,9% of respondents declared having been treated for alcohol abuse [5].

In addition to the early intervention and treatment scale up, the National Institute for Health Development (NIHD) has been co-ordinating a public awareness media campaign for over 10 years. In 2017, a campaign was initiated aiming to help risky drinkers to reduce their alcohol consumption, within the programme “Sober and Healthier Estonia”, and thereby avoid the harmful consequences of their drinking patterns. The campaign’s call to action directed people to conduct the AUDIT test [6] on the alkoinfo.ee webpage. Depending on their test score, respondents were provided with recommendations and links to further reading. After the campaign, 20% of the adult population and 30% among the primary target group (people ages 25–45 who consume alcohol above a low-risk level) were aware that they could self-evaluate their personal alcohol consumption using the AUDIT test. During this 2017 campaign, 70,324 visitors visited the website www.alkoinfo.ee where information on all stages of changing drinking behaviour is available, while 60,842 completed the AUDIT test on the alkoinfo.ee website [7]. Thus, the campaign spurred some action by 6,5 and 5.7% of the Estonian population over 18 years old, respectively. To expand this success and more effectively decrease alcohol misuse over the internet, the *“Selge” program* (the word“selge” has the double meaning of being clean and sober in Estonian), a minimal-guidance self-help program adapted from the “takecareofyou” program developed in Switzerland [8, 9] was developed in 2018.

According to a recent individualized-participant data meta-analysis, participants receiving internet interventions based on personalised (normative) feedback are significantly less likely to maintain low-risk drinking patterns at follow-up than those in extended internet programs based on integrated therapeutic principles like Cognitive Behavioral Therapy (CBT) and Motivational Interviewing (MI) [10]. Moreover, guided internet interventions exhibited greater effects on drinking patterns than unguided interventions [10]. However, only one study has directly compared a brief online intervention conceptualised as PNF (Personalized Normative Feedback) and a booklet with an unguided online self-help intervention. Although unguided, the latter was very intense, containing 56 daily sessions plus six weekly follow-up sessions, and involved alcohol misusers from the general population [11]. Although only 8 % completed all sessions in the intensive intervention group, there was a superior reduction in alcohol use in this group than in the PNF/booklet group over the medium term (6 months follow-up).

The goals of the currently-proposed study are to evaluate the efficacy of the adapted *“Selge” program*, in terms of reducing alcohol misuse in Estonians, and to assess its effects on treatment referrals. The intervention is adapted from the integrated alcohol misuse and depression symptoms treatment developed by collaborators [12] and consist of 10 modules based on MI and CBT. We expect that the *„Selge* “*program* will result in greater reductions in alcohol misuse than the control intervention, which will consist of a self test for alcohol abuse and routine advice regarding treatment.

## Methods

### Study design

The minimal-guidance Web-based self-help *“Selge” program* will be evaluated within a two-arm non-blinded randomized clinical trial (RCT). Eligible individuals will be randomized to either the online program or the control group (described below). Assessments will occur before randomization (T0; baseline), at 8 weeks (T1; treatment end), and at 6 months (T2; 4-month post-treatment follow-up). We have chosen these three measurement dates to distinguish intervention effects from possible follow-up effects. The control condition website will be accessible to both study conditions, and the actual use of treatment from usual resources assessed at T1 and T2. Participants will be made aware to which treatment arm they have been assigned after their baseline measurement. Participants allocated to the control condition will be provided with access to the full online program after they complete their final follow-up assessment.

### Data collection

Recruitment of study participants started on March 13th, 2019 and data collection will be continued through October 2019. Our aim is to recruit alcohol misusers from the Estonian general population through various means. Individuals are being recruited through several means across the country, including ad banners in web media platforms (Facebook, Instagram, Google search) and printed flyers in co-operation with general practitioners. A research institution press release was published by several local and one countrywide newspaper, and reported by one radio channel. Ad banners and publications invited people who would like to decrease their level of alcohol use to visit the research institute homepage for more information.

### Inclusion and exclusion criteria

To strengthen external validity, we applied very few inclusion/exclusion criteria. The main target group is Estonians with at least moderate misuse of alcohol. Inclusion criteria for participation are: 1) a minimum age of 18 years; 2) alcohol misuse, according to the Alcohol Use Disorder Identification Test (AUDIT score of ≥8); 3) at least weekly access to the internet; and 4) literacy in the Estonian language. Exclusion criteria are: 1) use of other psycho-social or pharmacological treatments to reduce the consumption of alcohol, opioids, stimulants or cannabis at baseline; 2) use of opioids, stimulants or cannabis more than four times over the previous 30 days; 3) previous treatment for cardiovascular problems; 4) pregnancy or breast feeding; and 5) suicidal ideations or plans within the last couple of years. Applicants who do not fulfill the criteria are informed that they do not fit the study but can still use the tool.

### Informed consent procedure

Interested individuals are invited by a link to the study website (see Fig. 1). The corresponding landing page includes all pertinent study information and an informed consent page. Before consenting, individuals are told: 1) the inclusion/exclusion criteria of the study; 2) the potential risks/benefits of completing the intervention; 3) safety arrangements for during and after the study; 4) that participation is voluntary; and 5) that the study has been approved by the Tallinn Medical Research Ethics Committee. Participants are instructed in how to create a user account the *“Selge” program* and provided contacts to researchers for if they have any trouble. Informed consent is obtained by having individuals check several boxes, confirming that they have read and understood the terms of research. They also are asked for their telephone number, so we can call them for follow-up in case they ignore the prompts delivered by e-mail. To register an account, they need to create a username and indicate their email address. An automatic email with a confirmation link completes the registration process, after which the baseline assessment starts.

**Fig. 1 Fig1:**
[figure not shown]
Web site landing page (translated from Estonian to English for publication purposes only)

### Randomization and trial flow

The baseline assessment starts with a suicidality screener [13]. Users indicating a higher risk of suicidality are excluded from the study and program and provided with a list of help lines. Users who do not meet the requirements for AUDIT are excluded from the study, but remain free to use the program, nevertheless. Users who fulfill the requirements after the baseline assessment are considered study participants and randomly assigned by a simple server randomization in a 1:1 ratio to either the *“Selge” program* or the control condition (see Fig. 2), informed about their assignment, and given further instructions. Participants in the control group are informed that they can use the program after 6 months, and provided with a help page — “Where to turn” — which is described in detail later in this paper. After 8 weeks (end of treatment), both groups undergo an assessment, as well as 6 months after baseline. An email prompt is sent automatically for each assessment, followed by two additional reminders sent to those who still have not completed the assessment. The last reminder sends a system email to the non-blinded study coordinator who then tries to contact the participant by phone up to twice. Participants are not compensated for completing the follow-up assessments. However, from all participants who complete all assessments, ten will be randomly selected to win a smartphone.

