#### Measures

Table 2 provides a schedule for each assessment measure. Demographic information will include age, gender, nationality, type of settlement (which major city or rural settlement), educational level, and the type of social engagement (employer, employed, student, retired, unemployed). All self-report questionnaires will be administered online.

**Table 2 Tab2:** Schedule of Assessment Measures

Self-Report Measures	Baseline (T0)	8 weeks (T1)	6 months (T2)
1. Demographics	x		
2. Suicidality Screener (P4)	x		
3. Alcohol Use Disorder Identification Test (AUDIT, main outcome)	x	x	x
4. Self-reported number of standard drinks on typical week over the past 6 months	x	x	x
5. Self-reported number of alcohol-free days on a typical week over the past 6 months	x	x	x
6. Drinking Motives Questionnaire (DMQ-R-5)	x	x	x
7. Motivation for Change	x	x	x
8. Mental Health Inventory (MHI-5)	x	x	x
9. Drug Use (NIDA ASSIST)	x	x	x
10. Customer satisfaction (iCSQ-8)		x	
11. Usage of other resources for intervention or treatment of alcohol use disorders		x	x

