##### Primary outcome

The primary outcome will be the change in the Alcohol Use Disorders Identification Test (AUDIT [6]) score between the 6-month follow-up and baseline assessments. The AUDIT is a 10-item self-report measure designed to assess alcohol misuse. Overall, the measure provides an indication of both alcohol use and alcohol-related problems. The AUDIT is a widely used, reliable, and validated estimate of alcohol misuse [6].

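### No follow-up step described asks 6-month non-responders for the 10-item AUDIT alone, although only 40–60% are expected to respond

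*Protocol article*

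**What the plan says.** The contact sequence is in the protocol article under Randomization and trial flow. Each assessment starts with an automatic e-mail prompt, "followed by two additional reminders sent to those who still have not completed the assessment". The last reminder alerts the non-blinded study coordinator, "who then tries to contact the participant by phone up to twice". Under Informed consent procedure, the phone number is requested "so we can call them for follow-up in case they ignore the prompts delivered by e-mail". The only incentive is tied to full completion: "from all participants who complete all assessments, ten will be randomly selected to win a smartphone".

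On mode, the Measures section states: "All self-report questionnaires will be administered online". Table 2 gives the schedule. At T2 it lists the AUDIT, standard drinks, alcohol-free days, drinking motives, motivation for change, MHI-5, drug use, and use of other resources.

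On the primary outcome: "The AUDIT is a 10-item self-report measure designed to assess alcohol misuse", and the endpoint is the change in its "score between the 6-month follow-up and baseline assessments".

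The Discussion names the phone calls as the measure taken against loss to follow-up, and with them in place expects follow-up of 50–70% at 8 weeks and 40–60% at 6 months.

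**The concern.** The primary endpoint needs one short instrument at T2. The reminders seek completion of the whole assessment, and no step described lowers the request to that instrument for someone who has not answered. Some people who will not work through eight measures might still answer ten questions, and the article describes no route for them.

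The stakes are moderate. Roughly half of the primary outcomes are expected to be missing and are to be imputed. Stopping the program and not answering T2 plausibly go together, although the article does not say so. Each AUDIT score obtained from a participant who would otherwise be lost adds information and reduces the share of the primary result that rests on the imputation model.

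**Working it through.** **What the follow-up route asks for**

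| Step | What the article says is sought |
|---|---|
| E-mail prompt and two reminders | Completion of the assessment |
| Up to two phone attempts | Not stated |
| Mode | Online for all self-report questionnaires |
| Partly completed assessment | Not stated whether it is kept |
| AUDIT-only request | None described |

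Table 2 rows marked at T2 are rows 3 to 9 and row 11, which makes 7 + 1 = 8 measures. The AUDIT is the first row with a follow-up entry, but the table is not said to give the order of presentation.

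**Inputs**

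- d = 0.23, 80% power, α = 0.05 (Sample size calculation)
- two-sided testing (Data analysis plan)
- 1:1 allocation (Randomization and trial flow)
- target of 600 (Abstract)
- T2 follow-up of 40–60% (Discussion)

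**Reproducing the plan's own figure**

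Normal approximation: n per arm = 2(1.960 + 0.842)² / 0.23² ≈ 297. The two-sample t-test gives 297.7, rounded up to 298 per arm, so N = 596 as stated. This figure contains no allowance for attrition.

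**Power at the expected follow-up**

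With 600 randomised and equal follow-up f in both arms, n per arm = 300f, and power ≈ Φ(d·√(n/2) − 1.96). At f = 0.50, n = 150, 0.23 × √75 = 1.992, and Φ(0.032) = 0.513. The exact t-test values are:

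| T2 follow-up | Observed AUDIT scores | Power at d = 0.23 |
|---|---|---|
| 40% | 240 | 0.427 |
| 45% | 270 | 0.469 |
| 50% | 300 | 0.510 |
| 55% | 330 | 0.549 |
| 60% | 360 | 0.586 |
| 65% | 390 | 0.620 |
| 70% | 420 | 0.652 |

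**What a short form could add**

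The documents give no recovery rate, so 5–10 percentage points is an assumption. Five points are 0.05 × 600 = 30 scores, and ten points are 60. At 50% follow-up there are 300 non-responders, so this means 10% to 20% of them accepting the short form.

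- From 40%: power goes from 43% to 47% (+5) or 51% (+10).
- From 50%: from 51% to 55% or 59%.
- From 60%: from 59% to 62% or 65%.

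At 50% follow-up, the number of primary outcomes to be imputed falls from 300 to 270 or 240.

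**The case against.** A reader might infer that non-responders are pursued only for the full battery, and that anyone willing to give the AUDIT but nothing more therefore yields no primary outcome. The article does not support that. It does not say what the coordinator asks on the phone, and online administration as the general mode does not settle it. Nor does it say that an unfinished assessment is discarded or that the AUDIT comes late. Page-by-page saving is described only for the treatment modules, but the questionnaires may work the same way. A condensed article may also leave call scripts and partial-data rules to the full protocol. This objection stands in full, and it limits the point to what the described procedure lacks.

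The burden is also smaller than eight measures suggests. Drinks and alcohol-free days are two self-reported counts, motivation for change is 3 items and the MHI-5 is 5. The non-response problem that the article names is ignored e-mails, and a shorter form does nothing for someone who never opens the message. That is a fair limit on the likely yield.

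The power figures are for complete cases, whereas multiple imputation is planned, with complete cases as a cross-check. The figures show scale and do not predict the power of the planned analysis.

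Finally, a short form offered too early could divert people who would have completed everything. That is a reason to place it last, not to leave it out.

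**Conclusion.** This is a minor and inexpensive improvement to the follow-up procedure, not an error in the plan. The procedure described contains no request for the primary outcome alone, while 40–60% of participants are expected to be missing at T2 even with the calls.

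The size of the gain is unknown. Assuming 5–10 points of T2 follow-up are recovered, equal follow-up in both arms and d = 0.23, complete-case power with 600 randomised rises from about 51% at 50% follow-up to about 55–59%. Even 70% follow-up gives only about 65%, so the measure would not restore 80%. The missing attrition allowance in N = 596 is a separate matter that a short form would ease but not solve. The other benefit, fewer imputed primary outcomes, does not depend on the power figures, though its size depends on the same unknown recovery rate.

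**What to change.** Add one last step at T2 only. Once the final reminder and the call attempts have not produced a completed assessment, send participants in both arms a link to an AUDIT-only form that they complete themselves online. This keeps the mode of collection and avoids an interview by the non-blinded coordinator. Record which form each participant used, and count a submitted AUDIT for the primary outcome even if the other measures are unfinished.

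Also state what the phone calls collect, whether partly completed assessments are kept, and where the AUDIT stands in the order of questionnaires. If the AUDIT already comes first and is already saved, only the last message is new. Say whether an AUDIT-only response counts for the prize draw.

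The cost is one short form and one added message on the existing website, with no extra staff. Some late responders will have no secondary measures. Recruitment had already begun when the article was written, so the step would come in during the trial and should start at the same time in both arms.

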**Fig. 2 Fig2:**
[figure not shown]
Randomization and trial flow chart

### Intervention and control condition

#### Treatment condition (“Selge” program)

The treatment website encompasses a dashboard, a drinking diary, 10 treatment modules and the help page “Where to turn?” (see control condition).

##### Modules

Ten treatment modules (see Fig. 3) comprise the majority of this 8-week program. Participants are advised to complete the modules at their own pace, but in the order listed. However, they may freely skip or repeat any module, if they choose. The content of each module was created based upon the principles of CBT and MI (Table 1). The emphasis is on strategies to reduce negative thinking and worry, on behavioural activation, and on self-care (e.g., sleep hygiene). A progress bar, also visible on the dashboard, indicates each user’s progress in the module, which is saved page by page.

**Fig. 3 Fig3:**
[figure not shown]
Main menu of intervention modules (translated from Estonian to English for publication purposes only)

**Table 1 Tab1:** Overview of Module Content

Module Number and Title	Module Content
M1: Introduction	• Introduction to the intervention • Motivational enhancement (i.e., identifying reasons for change, and pros and cons of drinking and not drinking) • Self-monitoring alcohol use and mood
M2: Strategies for Meeting Your Goals	• Strategies to change drinking habits, including stimulus control (e.g., ridding home of cues) • Resisting alcohol in specific situations (e.g., situations involving negative emotions) • Practicing refusal skills in high-risk situations • Developing personal strategies to reduce/abstain from harmful alcohol use
M3: Learning to “Say No” to Alcohol	• Learning about the various ways to say no to alcohol. • Ways to resist social pressures to drink • Trying out a few role-plays to practice drinking-refusal skills
M4: Identifying Risky Situations	• Identifying personal high-risk situations for drinking • Learning about “seemingly unimportant decisions” that could lead to heavy drinking
M5: Problem Solving	• Relating mood/alcohol issues to problems • The difference between controllable and uncontrollable problems • Formal problem solving (including problem identification, generating possible solutions, evaluating possible solutions, selecting a course of action, and evaluating the implementation of an action plan)
M6: Coping with Craving	• Psychoeducation about craving (e.g., different forms of craving [mental and physical]) • Introduce self-monitoring of craving • New ways to effectively cope with cravings (e.g., distraction, talking, experiencing the craving, and recalling the negative outcomes of drinking)
M7: Dealing with Slips	• Define a “slip” versus a full-blown relapse • Introduce ways to cope with slips in mood and/or drinking
M8: Meeting Your Needs	• “Sleep Hygiene” • Ruminating and worrying less • Increasing and/or improving social network
M9: Relaxation Exercise	• Key relaxation exercises to reduce stress (i.e., progressive muscle relaxation) • Deep breathing • Scheduling relaxation times during the week
M10: Preserve Your Success	• Identify “early warning signs” for slip/relapse • Create a personalized relapse-prevention plan • Discuss ways to cope with relapse • Identify top five coping strategies

